## **Work package 3:**

**Objective 3: Validation of proteomic analysis**

The proteomics work package aims to develop a second stage test for distinguishing benign and malignant adnexal masses using liquid chromatography (LC) and MALDI-based mass spectrometry. It will continue seamlessly the work that is currently being done in our pilot study. The pilot study consists of a set of 39 serum samples, 20 benign samples and 19 malignant samples which are being analysed using MALDI-TOF based proteomic profiling. After proper processing of the data, mathematical and probabilistic methods will be used to develop models based on a panel of  $m/z$  peaks. The combination of  $m/z$  peaks with the highest diagnostic performance will constitute the PILOTMODEL. This workpackage aims to (1) expand the number of samples analysed and (2) validate the PILOTMODEL. This will be accomplished by making use of the state-of-the-art mass spectral analysis capabilities that have recently become available to us at the Katholieke Universiteit Leuven through the foundation of the Interfaculty Centre for Proteomics and Metabolomics (ProMeta).

The number of samples will be increased by 100 and this new set of patients will be called the prospective data set. The additional proteomics experiments will be carried out on set of patients which reflect the distribution of benign and malignant samples. Then, after proper processing of the data, this set of patients will be used to assess the predictive performance of the PILOTMODEL. If unsatisfactory this set of patients can be used to further improve and refine the PILOTMODEL. This entails the identification and verification of the proteins and/or peptides that are part of the diagnostic model with the best discriminatory performance. The identification allows to replace the  $m/z$  values by their corresponding biomolecules and allows to decouple the model from mass spectrometry.

Hereby we will make use of mathematical and probabilistic methods that model the data and predict clinically relevant classes. First, pre-processing techniques will be developed and used to allow comparisons between spectra. Next, both univariate and multivariate techniques will be used to develop models that are able to distinguish benign from malignant neoplasms. This will be accomplished by using both standard and advanced statistical and mathematical data analysis techniques (e.g. logistic regression, LS-SVMs, Bayesian networks). This work package is further subdivided in 3 tasks:

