### **O3: Validation of proteomic analysis**

**Pilot study.** We adopted the MALDI approach to benefit from the potential diagnostic power of mass spectrometry-based proteomics. We have started a pilot study consisting of 39 serum samples from 20 patients with benign ovarian masses and 19 patients with malignant ovarian masses. The patients in the malignant group consist of 3 stage I tumours, 15 stage III tumours and 1 stage IV tumour. In this first phase the goal is to detect interesting m/z ranges that display differential patterns in benign and malignant ovarian cancer (PILOTMODEL). Subsequently, a second phase consisting of identification of proteins and/or peptides within these mass ranges will be initiated. The use of MALDI-TOF offers a wide range of advantages compared to the SELDI platform described earlier. It provides a better resolution and wider mass range compared to the SELDI platform. Secondly MALDI offers the possibility of identifying interesting peaks at key m/z values by subsequent fragmentation which is impossible with SELDI. The resulting mass spectral patterns can be submitted to mass spectrum interpretation engines such as MASCOT for comparison with known proteins and peptides in databases, returning the most probable biomolecule responsible for the mass spectral measurement.

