### **Task 3.1: Sample collection for proteomics second stage test**

The aim is to test the clinical application of proteomics for the pre-operative classification of ovarian tumours. The following protocol is being used to collect samples where approximately 100 patients with an adnexal mass will be recruited and studied within 35 days before investigative surgery. Medical and family histories will be recorded. A sample of peripheral venous blood will be taken for the proteomic analysis. Findings at surgery and the histological classification of excised tissues as malignant or benign (and by cell type) will be used as outcome measures. Informed consent must be signed before collection of blood sample. Standard blood clotting tubes without any anti-coagulantia are used for the collection of serum samples. Venous blood is collected in an 8-10 ml clotting tube, this will yield  $\pm 3-4$  ml serum. Samples are collected by adequately trained medical personnel only (nurse or doctor). Once the blood is taken, the tube is mixed gently end over end. The tubes are placed in a plastic bag (per donor) and placed at 4°C before and during transport to the laboratory. The maximum allowed time between collection and preparation of the serum sample is 3 hours.

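### Work package 3 does not tie its 100 proteomics samples to difficult masses, and it lets the set that tests PILOTMODEL also refine it without naming independent data for the refined model

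*Protocol*

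**What the plan says.** **Purpose.** Work package 3 states: "The proteomics work package aims to develop a second stage test for distinguishing benign and malignant adnexal masses". Task 1.5 defines who needs such a test: the 15% of masses nearest the LR1 decision boundary, expected to be about 300 patients.

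**Development data.** "The pilot study consists of a set of 39 serum samples, 20 benign samples and 19 malignant samples". Of the cancers, the O3 section on the consortium's own work says: "The patients in the malignant group consist of 3 stage I tumours, 15 stage III tumours and 1 stage IV tumour".

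**Prospective data.** "The number of samples will be increased by 100 and this new set of patients will be called the prospective data set". On their selection: "The additional proteomics experiments will be carried out on set of patients which reflect the distribution of benign and malignant samples". Task 3.1 adds: "approximately 100 patients with an adnexal mass will be recruited and studied within 35 days before investigative surgery". Neither sentence mentions difficulty. Section 7 (Serum tumour markers) takes proteomics blood by centre. By contrast, Task 4.1 limits marker sampling to tumours that need a second-stage test.

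**Use of the prospective data.** The set first assesses PILOTMODEL. Then: "If unsatisfactory this set of patients can be used to further improve and refine the PILOTMODEL". The protocol does not define what counts as unsatisfactory, and it names no further hold-out set, resampling scheme or cohort for the refined model.

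**The concern.** There are two separate problems.

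**Population.** A second-stage test has to work in masses that the first stage leaves unresolved. The O6 section on the consortium's own work reports that borderline tumours are three times as common among uncertain masses as among the others. It also reports that experts classified 60% of borderline tumours correctly (33/55), against 96% of primary invasive tumours (162/169). The pilot cancers are mostly advanced: (15 + 1)/19 = 84% are stage III or IV. A model built on these and tested mainly on masses that are easy to classify could look good without showing anything about the masses that need the test.

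**Reuse.** Once the 100 samples have been used to choose or re-weight peaks, they can no longer give an unbiased estimate for the resulting model. With high-dimensional spectra and about 26 malignant samples, the optimism could be large.

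**Working it through.** **The protocol's own figure.** Task 1.5: 15% × 2,000 = 300 difficult masses. This reproduces. The pilot total also agrees: 20 + 19 = 39. Work package 3 gives no precision or power basis for its 100 samples, so there is nothing further to reproduce.

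**Inputs.**
- Share of difficult masses: 15% (Task 1.5, LR1 rule), or 8% by examiner judgement (O6, consortium section: 90/1066 = 8.4%; 39/507 = 7.7%).
- Malignancy prevalence, from the denominators in the same section: 266/1066 = 25.0%; 143/507 = 28.2%; pooled 409/1573 = 26.0%.

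**Step 1: difficult masses among 100, reading Task 3.1 literally.**
- 15% rule: 100 × 0.15 = 15. Malignant: 15 × 0.25 to 0.28 = 3.8 to 4.2, about 4, leaving 11 benign.
- 8% rule: 100 × 0.08 = 8. Malignant: 8 × 0.25 to 0.28 = 2.0 to 2.2, about 2, leaving 6 benign.
- Over-representation of borderline tumours could raise the malignant share. As an assumed upper case, half of the 15 gives about 8.

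**Step 2: what those numbers can show** (exact Clopper-Pearson 95% intervals; the observed counts are illustrative).

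| Set | Sensitivity | Specificity |
|---|---|---|
| 15 difficult, 4 malignant | 3/4: 19% to 99% | 9/11: 48% to 98% |
| 8 difficult, 2 malignant | 2/2: 16% to 100% | 5/6: 36% to 99.6% |
| 15 difficult, 8 malignant (assumed) | 6/8: 35% to 97% | 6/7: 42% to 99.6% |
| All 100, 26 malignant | 21/26: 61% to 93% | 59/74: 69% to 88% |

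The whole set gives a usable estimate for adnexal masses in general. The difficult subset does not.

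**Step 3: optimism if the same 100 samples refine the model.** Simulation with 26 malignant and 74 benign samples and peaks that are pure noise. The five peaks with the strongest single-peak AUC are chosen, a logistic model is fitted, and its AUC is computed on the same samples. The true AUC is 0.50. The protocol gives no number of peaks, so a range is assumed.

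| Noise peaks (assumed) | Mean apparent AUC | Mean AUC in new data |
|---|---|---|
| 50 | 0.78 | 0.50 |
| 200 | 0.83 | 0.50 |
| 300 | 0.84 to 0.85 (two sets of runs) | 0.50 |

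**Step 4: recruitment if all 100 were to be difficult masses.** 100/0.15 = 667 patients, or 100/0.08 = 1,250, from the three centres listed for proteomics under Study objectives, with every difficult case sampled.

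**The case against.** **The 100 samples may be meant as difficult masses.** The O3 section on the consortium's work speaks of analysing more patients by mass spectrometry as a second-stage test. The O6 section lists proteomics among the options for difficult masses, the Duration section counts it among the second-stage tests, and Task 3.1 has second stage in its heading. The distribution that the set should reflect could even be that of difficult masses. This stands: a reader might infer that the protocol deliberately chose unselected masses, but it does not say so. What remains is that the two sentences governing recruitment omit a criterion that Task 1.5 sets and Task 4.1 writes out, and they pull against the second-stage framing.

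**PILOTMODEL is independently tested.** Task 3.3 builds it on the pilot data and validates it on the prospective data, and refinement comes only afterwards and conditionally. This also stands. A reader might conclude that Work package 3 validates nothing, which goes too far: the gap concerns the refined model only. Nor does the protocol say that a refined model would be reported as validated, and refinement fits the stated aim of developing a test.

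**Details may lie in an unseen SAP.** Locking of the cut-off and fold-wise peak selection may well be there. The point does not rest on their absence. It rests on the reuse that the protocol permits and on its recruitment wording.

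**The fall in AUC from 0.88 to 0.73.** A reader might cite this drop, reported in the O6 section, against the current difficult-tumour model. It belongs to an earlier model built on 54 uncertain cases with papillary projections. The current model is reported at 0.85 on both development and test sets.

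**Conclusion.** The point holds in two limited parts and should be acted on.

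1. Work package 3 leaves its study population unresolved. If its recruitment text is followed literally, about 8 to 15 of the 100 samples are difficult masses, with about 2 to 4 malignant, and second-stage sensitivity cannot be estimated. This assumes that the 100 follow the general case mix and that difficult masses have the overall malignancy prevalence. A malignant share of one half still leaves an interval of 35% to 97%. If the 100 are in fact all difficult masses, this part reduces to a wording conflict.
2. A refined PILOTMODEL would have no independent validation in the protocol. The simulated apparent AUC of 0.78 to 0.85 for noise assumes 50 to 300 peaks and evaluation on the samples used for selection. It shows how large the optimism could be and is not a forecast for this study.

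The test of the unrefined PILOTMODEL in adnexal masses generally is not affected.

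**What to change.** - Reconcile the recruitment text of Work package 3 and Task 3.1 with Task 1.5. Give priority to sera from masses that meet the second-stage trigger at the three centres, and top up with other masses if too few are available.
- Report PILOTMODEL performance separately in difficult masses, with exact intervals, and base any second-stage claim on that subgroup alone.
- Fix PILOTMODEL, its cut-off and its pre-processing before the prospective spectra are linked to histology. Define in advance what counts as unsatisfactory, and report this validation once.
- Label any refit as development. Take its performance from cross-validation that repeats peak selection in every fold, and do not call it validated without new data.

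**Cost.** The number of assays is unchanged. Collection may be slower. Requiring all 100 to be difficult masses would not be cheap (667 to 1,250 patients at three centres). Yield would be lower still because Task 1.5 requires only one second-stage test and the O6 section leaves the choice to the investigator. Topping up is therefore likely, and intervals in the difficult subgroup will be wide. A refined model loses any claim to validation within this study.

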### **Task 3.1: Sample collection for proteomics second stage test**

The aim is to test the clinical application of proteomics for the pre-operative classification of ovarian tumours. The following protocol is being used to collect samples where approximately 100 patients with an adnexal mass will be recruited and studied within 35 days before investigative surgery. Medical and family histories will be recorded. A sample of peripheral venous blood will be taken for the proteomic analysis. Findings at surgery and the histological classification of excised tissues as malignant or benign (and by cell type) will be used as outcome measures. Informed consent must be signed before collection of blood sample. Standard blood clotting tubes without any anti-coagulantia are used for the collection of serum samples. Venous blood is collected in an 8-10 ml clotting tube, this will yield  $\pm 3-4$  ml serum. Samples are collected by adequately trained medical personnel only (nurse or doctor). Once the blood is taken, the tube is mixed gently end over end. The tubes are placed in a plastic bag (per donor) and placed at 4°C before and during transport to the laboratory. The maximum allowed time between collection and preparation of the serum sample is 3 hours.

### **Task 3.2: LC-MALDI Mass spectrometry**

Mass spectrometric measurements are carried out in the gas phase on ionized analytes. By definition, a mass spectrometer consists of an ion source, a mass analyser that measures the mass-to-charge ratio ( $m/z$ ) of the ionized analytes, and a detector that registers the number of ions at each  $m/z$  value (Aebersold and Mann, 2003). The ion source is known as Matrix Assisted Laser Desorption/Ionization (MALDI). Its function is to volatilise and ionise the proteins and peptides for further analysis. It does this by using laser pulses to desorb and ionise the molecules under study out of a dry, crystalline chemical matrix. The mass analyser is based on a Time-Of-Flight tube design (TOF) and allows for single MS measurements to be performed. For identification of molecules two TOF analysers are used in a tandem MS setting which allows for the fragmentation of the proteins under study. For biomacromolecules such as proteins, fragmentation into smaller peptide fragments is a prerequisite for reliable identification.

### **Task 3.3: Pre-processing and mathematical modeling (*in silico* analysis)**

The analysis of mass-spectrometry data is far from straightforward because of its high dimensional nature. It is virtually impossible to manually analyse results and search for interesting diagnostic proteins and/or peptides.

Therefore advanced methods that draw from statistics, machine learning, probability theory and mathematics are necessary to analyse the data that results from MALDI-TOF/TOF. Furthermore, the analysis is subdivided in two steps corresponding to two objectives in this work package: pre-processing and model development.

**Pre-processing:** The goal of pre-processing is to account for time and mass disturbances between spectra of different samples. Peaks in the mass spectrum correspond to individual proteins or peptides (or fractions thereof) and their peak heights are related to their concentration. When analysing mass spectrometry data for biomarker discovery only a subset of peaks that result from ionisation of biomolecules such as peptides or proteins are biologically significant and of use in applications. In order to detect and locate these peaks, the raw data is subjected to several pre-processing steps: base line correction, smoothing, peak detection and peak alignment. Base line correction and smoothing can be handled using filtering methods and curve fitting techniques. Peak detection and alignment will be handled using wavelet analysis. Wavelets have been widely used to de-noise signals in several number of contexts (e.g. magnetic resonance, ultrasound blood flow and computed tomography) and can be used to extract desirable features from the data. This results in the location of peaks and their quantification by combining elements from signal processing with wavelet analysis.

**Model development:** The pilot data set will be used to develop a model (i.e. PILOTMODEL) which will subsequently be validated using the prospectively collected data from this project. Both univariate and multivariate data analysis will be used for model development on the pre-processed data. Univariate data analysis will be used to look for single diagnostic peaks. For this purpose, non-parametric statistics will be used (i.e. Wilcoxon rank sum tests). Moreover the predictive performance of each single peak will be estimated using sensitivity, specificity, Area Under the ROC curve (AUC) and likelihood ratios. We expect that a single biomarker will be unsatisfactory to accurately discriminate benign and malignant ovarian cancer. Therefore multivariate analysis will be performed. This will allow to develop a panel of peaks which may have poor predictive performance in a univariate approach but reach significance when combined with other peaks. For this purpose we will use both standard and advanced mathematical techniques. Currently we plan to use stepwise logistic regression, Least-Squares Support Vector Machines and Bayesian network analysis. These three methods have already proven their usefulness in medical and biological data analysis and offer a complementary view on the data.

#### **Work package 4:**

##### ***Objective 4: Validation of new set of tumour markers***

External validation is needed to test the added value of combinations of novel tumour markers to the standard clinical and ultrasound variables in patients with adnexal tumours. Therefore, two tasks have to be executed:

#### **Task 4.1: Data collection**

In tumours needing a 2nd stage test in order to make a reliable preoperative diagnosis, a blood sample is taken and later on a combination of the following markers will be assessed:

1. CA 125 II
2. CA 15-3
3. CA 72-4
4. CEA
5. macrophage colony-stimulating factor (M-CSF)
6. HE4
7. Mesothelin
8. Osteopontin
9. kallikrein(s)

However, if in the meantime more promising markers are proposed, some of these markers may be replaced by others.

## Task 4.2: Validation of the model

Similarly as to the validation of 2nd stage tests in WP2, each new tumour marker will be assessed using a case-control study design with tumours where a new marker was present considered as “cases” and difficult masses present in the data of IOTA 1, 1b and 2 that match the “cases” in type of tumour and patient’s age (<50 versus ≥50) considered as “controls”. Each new tumour marker will be validated in terms of possible increased sensitivity or specificity.

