### **O4: Validation of a new set of tumour markers**

We prospectively assessed the value of serum CA-125 [50-51]. These studies challenged the current clinical practice, where CA-125 is an integral part of the preoperative work up of patients with adnexal masses. These studies proved for the first time that a single measurement of serum CA-125 does not add to the diagnostic confidence of experienced ultrasound examiners nor to the diagnostic performance of logistic regression models to distinguish between benign and malignant tumours. Therefore, we need to test combinations of new tumour markers that might really improve the classification of difficult tumours. A pilot study on proteomics has been performed in our consortium and this was first presented at the ESGO 2007 meeting (European Society of Gynaecologic Oncology) [52]. External validation is now needed to test the value of combinations of novel tumour markers with clinical and ultrasound variables in other patients with adnexal tumours.

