### **Task 2.2: Validation of the model**

The presence, the amount of vascularisation (colour score) and the pattern (regular or chaotic) of blood flow detected with colour Doppler and contrast-enhanced images will be investigated to assess whether the use of CnTI technology provides advantages with respect to the unenhanced ultrasound examination in the assessment of gynaecologic diseases, as seen in the preliminary results. Results will be validated using a case-control design. The above tumours for which intravenous contrast agents have been applied are considered as the “cases”. In IOTA 1, 1b and 2 a “historical control group” of difficult masses will be composed with two matching factors: 1) the same tumour type and 2) age (<50 versus ≥50). The difference in sensitivity and specificity of the investigator’s diagnosis between the cases with intravenous contrast and the control group will be assessed. The value of quantitative assessment of contrast ultrasound as second stage test in difficult tumours will also be compared with other second stage tests that were applied in the same patients.

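### Work package 4 asks what a combination of tumour markers adds to clinical and ultrasound data, but Task 4.2 assesses each marker singly against unpaired historical controls

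*Protocol*

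**What the plan says.** The opening of Work package 4 states the objective: "External validation is needed to test the added value of combinations of novel tumour markers to the standard clinical and ultrasound variables". It then says that two tasks serve this purpose, one for data and one for analysis.

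The consortium background for O4 gives the reason. A single CA-125 reading improved neither the confidence of experienced examiners nor the performance of logistic regression models, and so "we need to test combinations of new tumour markers that might really improve the classification of difficult tumours". The same paragraph closes by calling for a study to "test the value of combinations of novel tumour markers with clinical and ultrasound variables in other patients with adnexal tumours".

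Task 4.1 is worded to match. In masses that need a second stage test, "a blood sample is taken and later on a combination of the following markers will be assessed", followed by nine list entries.

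Task 4.2, headed as validation of a model, turns to single markers: "each new tumour marker will be assessed using a case-control study design with tumours where a new marker was present considered as" the cases. Controls are difficult masses from IOTA 1, 1b and 2, matched on tumour type and on age below 50 versus 50 or over. The measure is given per marker: "Each new tumour marker will be validated in terms of possible increased sensitivity or specificity".

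Task 4.2 says that it works like Work package 2, where Task 2.2 states: "The difference in sensitivity and specificity of the investigator’s diagnosis between the cases with intravenous contrast and the control group will be assessed".

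**The concern.** The objective and the analysis have different targets. The objective concerns a joint contribution: what several markers together add to information the clinician already has. The analysis concerns marginal contributions, one marker at a time, and reads them off a comparison between different groups of patients.

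This can mislead in two ways. A panel whose members are weak alone but informative together could be missed. A marker that discriminates well alone, but only repeats what ultrasound already shows, could be reported as useful. Second stage tests exist to help with masses that ultrasound leaves uncertain, so the second error goes to the purpose of the work package.

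**Working it through.** WP4 states no sample size, significance level or effect size, so there is no planned figure to reproduce. The check sets the texts side by side.

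1. **Target of the objective.** Let X be the clinical and ultrasound information on a patient and M the marker panel. Objective 4, and the O4 background, ask for performance(X + M) minus performance(X), in patients who have both.

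2. **Target of Task 4.2.** For each marker k, and separately for sensitivity and specificity, the contrast is performance in IOTA 3 masses with marker k minus performance in matched IOTA 1, 1b or 2 masses without it.

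3. **Do the results in step 2 give the quantity in step 1?** No, for three reasons.
   - They contain no term for M as a whole. Single-marker results do not determine the joint result: markers may overlap, so that the panel adds less than the parts suggest, or complement each other, so that it adds more.
   - The two sides of each contrast are different patients. Matching on tumour type and two age bands does not hold X fixed, so a difference cannot be assigned to the marker given that patient's ultrasound findings.
   - If the outcome is the examiner's diagnosis, as in Task 2.2, it may not contain the marker result, because Task 4.1 has the assays run later on the blood sample.

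4. **Does another part of the protocol supply step 1?** Section 10 (Statistical analysis) promises further models using newly added variables and lists logistic regression among its exploratory methods. It names no markers, panel, baseline predictor or comparison with and without markers. Section O6 of the background hopes for an optimal diagnostic algorithm, again without an analysis. By contrast, Task 3.3 (proteomics) expects one biomarker to be inadequate and therefore plans a multivariate panel. WP4 has the same rationale but no such step.

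5. **How many patients could support step 1?** Task 1.5 sends the 15% of masses nearest the LR1 decision boundary to a second stage test: 0.15 × 2,000 = 300. This is a ceiling for markers. Section 1 limits the marker work package to centres with ethical approval and consent, and section O6 lets investigators choose among second stage tests. The background gives 19 or 20 centres for phase 2, and the same centres are to take part in phase 3. That is at most 300/20 = 15 to 300/19 ≈ 16 difficult masses per centre on average, and fewer with markers.

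**The case against.** **A baseline exists.** By following Work package 2, Task 4.2 adopts a contrast of difficult masses with and without the test, and the historical controls were assessed without the new marker. This stands: a reader might infer that the plan has no clinical and ultrasound comparator at all, and that would be wrong. The comparator is crude, unpaired and not adjusted for the clinical and ultrasound findings, but the idea of added value is present.

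**The detail may lie in a statistical analysis plan that is not shown.** Task 4.1 speaks of a combination, section 10 allows new models, and Task 4.2 does not forbid a joint analysis. The composition of the panel, the fitting method and the resampling scheme could properly be left to that plan. This stands for the detail but not for the core. Task 4.2 is not silent: it twice fixes the single marker as the unit of analysis. A later plan that followed it would miss Objective 4, and one that followed Objective 4 would depart from it.

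**Two further inferences should be resisted.** A reader might say that WP4 repeats a design the protocol itself reports as having failed. The O4 background reports a negative result for one marker, CA-125, in studies that looked at its addition to examiners and to models; it does not describe the failure of a design. A reader might also attach a false-positive probability to nine markers judged on two measures. WP4 states no test and no significance level, markers compared with controls from one historical pool would not be independent, and the count is not firm: CA-125 was already studied, the kallikrein entry may be plural, and markers may be replaced. No such figure can be supported, and multiplicity would not measure this mismatch in any case.

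**Conclusion.** The concern holds. Objective 4, the O4 background and Task 4.1 point to combinations of markers, and the first two ask what they bring alongside clinical and ultrasound variables. Task 4.2, the only analysis in the work package, evaluates each marker alone against unpaired historical controls. Carried out as written, it would not answer the WP4 question.

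The size of the resulting error cannot be derived from the protocol. The conclusion rests on the wording alone, with no assumption about significance level, power or marker performance. It affects one of six work packages and can be put right in the analysis text, so it should be corrected but does not threaten the study as a whole. It is also separate from the merits of historical controls: with ideal controls, an analysis of one marker at a time would still leave the contribution of a panel unestimated.

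**What to change.** Rewrite Task 4.2 along these lines.

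- **Main comparison.** In the IOTA 3 difficult masses that have marker data, compare one clinical and ultrasound predictor, named in advance (LR1 or the difficult-tumour model), with the same predictor plus a small prespecified marker panel, in the same patients. Report the change in AUC, and sensitivity and specificity at a fixed cut-off.
- **Fitting.** Use penalised estimation and an internal validation scheme suited to the number of cases actually available. With about 15 or 16 difficult masses per centre at best, testing by leaving out one centre at a time should not be required.
- **Single markers.** Keep them as secondary, descriptive results.
- **Label.** Call the panel result development, since WP4 describes no existing marker combination to validate.

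If the sponsor prefers to keep Task 4.2 as it is, the alternative is to narrow Objective 4 and the matching O4 text to single markers.

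The cost is small. The blood samples are already planned, and Task 1.2 allows no missing clinical or ultrasound inputs other than CA-125. There are two drawbacks: the result can no longer be presented as validation, and its precision is limited because at most about 300 difficult masses are expected and only some of them will have markers.
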